**Manufacturing**

The scope of the quality control system for the item is the area surrounded by the thick line.

Materials, parts, components

The range surrounded by the dotted line is the process range of the following manufacturing plants.

Factory name:

Mayo Inazawa Research Institute Co., Ltd.

Factory location:

[name]

Manufacturing license number: 23BZ005022

Manufacturing license classification: General

Acceptance inspection of materials, parts and components

Manufacturing, processing and in-process inspection

Product inspection

Packaging/ labeling

Strage and shipping decision

Shipping

Packaging and labeling (Written in Japanese)

<Clinical trial device label (sample)>
[figure not shown]

The label should include the title of the clinical trial coordinating physician and the serial number of the transcutaneous electrical stimulator.

**Management method**

1) The clinical trial coordinating doctor will deliver the clinical trial equipment to the investigator of the conducting medical institution immediately after the start of the clinical trial.

2) The clinical trial equipment manager of the clinical trial institution properly manages the clinical trial equipment at room temperature according to the procedure manual provided by the investigator through the director of the clinical trial institution.

3) The investigator prepares a document explaining the storage conditions for supplying the investigational device, the expiration date, etc. Will be delivered to.

4) The investigator and the investigator confirm the device number to be treated, and if there is a problem with the treatment device, including during non-treatment, report the device number and the status of the problem, and replace or repair it. We will respond promptly if necessary.

**Implementation schedule and procedure**

The schedule for observation, inspection, and evaluation is shown in the table below. The investigator or the investigator will carry out observations and examinations according to the schedule. Items that can be carried out by the investigator, such as subject background surveys and clinical tests, may be carried out by the investigator under the control of the investigator. (See the schedule below)

|  | **Screening** | **0 week** | **2 weeks** | **4 weeks** | **6 weeks** | **8 weeks** | **10 weeks** | **12 weeks** | **Drop out** |
| --- | --- | --- | --- | --- | --- | --- | --- | --- | --- |
|  | Visit 1-2 | Visit 3 | Visit 4 | Visit 5 | Visit 6 | Visit 7 | Visit 8 | Visit 9 |  |
| IC | **○** |  |  |  |  |  |  |  |  |
| TdES |  | **①** | **②** | **③** | **④** | **⑤** | **⑥** |  |  |
| Blood pressure | **○** |  |  |  |  |  |  |  |  |
| Blood sampling | **○** |  |  |  |  |  |  |  |  |
| contrast-enhanced MRI | **○** |  |  |  |  |  |  |  |  |
| logMAR VA | **○** | **○** | **○** | **○** | **○** | **○** | **○** | **○** | **○** |
| ETDRS VA | **○** | **○** |  |  |  |  |  | **○** | **○** |
| HFA | **○** |  |  |  |  |  |  | **○** | **○** |
| Slit | **○** |  |  | **○** |  |  |  | **○** | **○** |
| IOP / fds | **○** |  |  | **○** |  |  |  | **○** | **○** |
| AEs | **○** | | | | | | | | |

**Abbreviations:** IC, informed consent; TdES, transdermal electrical stimulation; VA, visual acuity; HFA, Humphrey field analyzer; Slit, slit lamp examination; IOP, intraocular pressure; fds, fundus examination; AE, adverse event.

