# 0. Overview

| Title | A study on the safety and efficacy of transcutaneous electrical stimulation for non-arteritic ischemic optic neuropathy (Phase II / III study) |
| --- | --- |
| Purpose | To confirm the safety and efficacy of transcutaneous electrical stimulation using skin electrodes for patients with non-arteritic ischemic optic neuropathy for visual function after treatment. |
| Design | prospective, non-randomized, open-label, uncontrolled multicenter trial |
| Phase | Ⅱ/Ⅲ |
| Device | 1. Overview   This device is that a skin electrode for electrical stimulation is attached to the center of the forehead and the skin on the lower eyelid ear side of the target eye to give constant electrical stimulation under various conditions to treat retinal and optic nerve diseases.  Constitution  　It consists of an "electrical stimulator", a "skin electrode" and an "electrode connection cable" that connects them.   1. Specification 2. Electrical stimulation device  - Current 0～3 mA   ・Time 0～10 msec×2 biphasic  ・Inverval 50 msec   1. Skin electrode　（Sekisui Kasei Co.Ltd.）   ・Size　　　　19×38 mm  ・Element　　　Ag/Agcl  ・Base material　　　　　Non-woven fabric  ・Gel 　　　　Conductive adhesive gel   1. Capacitance   AC adapter rating (input)　AC 100 V　50/60 Hz　30 VA  AC adapter rating (output)　DC 5 V　4 A   1. Weight：700 g、Size： 225×165×40 mm |
| Inclusion Criteria | 1. Clinically diagnosed with NAION and age ≥20 years and ≤80 years  2. NAION patients who were determined to have fixed symptoms more than 6 months after the onset  3. Decimal visual acuity from hand motion to 0.7  4. Patients who provided signed consent with sufficient understanding after receiving an explanation of the responsibilities of participating in this trial  5. Regular hospital visits every 2 weeks for 12 weeks |

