| Exclusion Criteria | 1. Any of the following on a screening blood sampling test:  ・ ESR: more than 20 mm/h  ・ CRP: more than 10 mg/l  2. Patients with ocular disease other than ischemic optic neuropathy confirmed by contrast-enhanced MRI at the time of definitive diagnosis of non-arteritic ischemic optic neuropathy.  3. History of allergy to mydriatic agents and eye surface anesthetics  4. Presence of vitreous macular traction syndrome, macular edema, epiretinal membrane, myopia with posterior staphyloma, diabetic retinopathy, conjunctival inflammation, ocular infection, severe dry eye, grade 3 or higher Emery-Little grade cataract, and posterior capsule opacification  5. History or complications of a malignant tumor. However, patients with a history of malignant tumor that has not relapsed for more than 5 years were not excluded  6. Diagnosis of dementia or mental disorder with ongoing treatment  7. Diabetes mellitus (HbA1c [NGSP]> 10.0%)  8. Hypertension (systolic ≥ 180 mmHg and/or diastolic ≥ 110 mmHg) that is difficult to control even with oral treatment  9. Any of the following on a screening blood sampling test:  ・ Aspartate aminotransferase and alanine aminotransferase: more than three times the upper limit of the facility standard value  ・ Serum creatinine: more than 1.5 times the upper limit of the facility standard value  10. Ongoing treatment with ethambutol hydrochloride and/or amiodarone hydrochloride  11. Ongoing pregnancy, breastfeeding, or possible or planned pregnancy during the trial period  12. Participation in other clinical trials  13. Under investigational responsibility (shared) judged by doctors to be inappropriate for participation in this trial |
| Endpoints | ＜Primary endpoint＞  The logarithm of the minimum angle of resolution (logMAR) visual acuity  ＜Secondary endpoint＞  1. Changes in logMAR visual acuity  2. Changes in Early Treatment of Diabetic Retinopathy Study (ETDRS) visual acuity  3. Changes in mean deviation value of HFA 10-2  4. Changes in ccore of HFA monocular Esterman test scores  ＜Safety endpoint＞  The incidence of adverse events (AEs; type, frequency, and severity) |

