## 19) Intellectual property

20) Conflict of interest

Facility registration and case registration will be conducted by the central registration system in the Data Management Office, Clinical Trials Department, Chiba University Hospital.

1) The investigator will fax a copy of the approval notice of the clinical trial review committee and the facility registration request form to the case registration center after approval is obtained by the clinical trial review committee of the facility.

2) The Case Registration Center will register the facility and send a notification of completion of facility registration to the investigator.

1) The chief investigator or co-investigator obtains written consent and, as a result of the screening test, confirms that the subject meets the selection criteria and does not violate the exclusion criteria. The chief investigator, the co-investigator or collaborator will register the subject that the investigator or the investigator judges to be "qualified". Case registration is done on the website.

2) The chief investigator, co-investigator or collaborator will access the specified URL and enter the information required for case registration on the website. The chief investigator or co-investigator confirms the eligibility determination on the screen, and if it is determined to be eligibility, the protocol treatment is started. Once registered, the registration of the subject will not be cancelled. In the case of duplicate registration, the initial registration information (registration number) will be adopted in any case. If incorrect registration or duplicate registration is found, immediately contact the Data Management Office, Clinical Trials Department, Chiba University Hospital.

* The chief investigator or co-investigator must not perform protocol treatment until the subject is registered.

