**Safety and efficacy analysis**

Visual acuity (corrected decimal visual acuity converted to logMAR visual acuity is used to analyze the amount of change from baseline at week 12. A linear mixed-effects model is used as the statistical method, and the significance level of the hypothesis test is 5% on both sides. And the confidence interval is calculated as 95% confidence interval on both sides). If model analysis cannot be performed, only summary statistics are calculated. The detailed analysis method will be described in the statistical analysis plan.

Analysis of secondary efficacy endpoints included visual acuity (corrected decimal visual acuity converted to logMAR visual acuity and ETDRS visual acuity), static visual field test (HFA) 10-2 program and Estherman test (100 points). Perform statistical analysis. Multiplicity is not adjusted in the analysis of the secondary efficacy endpoint. A linear mixed-effects model is used as the statistical method, the significance level of the hypothesis test is 5% on both sides, and the confidence interval is 95% on both sides. If model analysis cannot be performed, only summary statistics are calculated. The detailed analysis method will be described in the statistical analysis plan.

For safety analysis, adverse events are aggregated, the number and proportion of cases of occurrence are aggregated, and a list is created for the presence or absence and severity of occurrence. In addition, the exact two-sided 95% confidence interval for the binomial distribution for the presence or absence of expression is calculated, and an appropriate significant difference test is performed as necessary.

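### The same investigator team may stimulate and measure the primary acuity endpoint, and the protocol does not keep earlier scores from the examiner

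*Protocol*

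**What the plan says.** - **Design.** The Overview describes a "prospective, non-randomized, open-label, uncontrolled multicenter trial" with 5 eyes of 5 patients at 3 sites. Eligible acuity runs from hand motion to decimal 0.7.
- **Primary endpoint.** The Overview names "The logarithm of the minimum angle of resolution (logMAR) visual acuity". Safety and efficacy analysis makes this specific: "corrected decimal visual acuity converted to logMAR visual acuity is used to analyze the amount of change from baseline at week 12". It adds that "the significance level of the hypothesis test is 5% on both sides".
- **Who examines.** Under Implementation schedule and procedure: "The investigator or the investigator will carry out observations and examinations according to the schedule". The following sentence allows delegation of items "such as subject background surveys and clinical tests, may be carried out by the investigator under the control of the investigator". The English text uses one word for what are evidently different roles.
- **Who treats.** The case-registration text, which follows the list of consent items, says: "The chief investigator or co-investigator must not perform protocol treatment until the subject is registered". This is a prohibition, but it implies that these roles give the treatment.
- **When.** The schedule table places logMAR acuity at screening and at every visit from week 0 to week 12. Stimulation is at weeks 0, 2, 4, 6, 8 and 10. ETDRS acuity is measured at screening, week 0 and week 12.
- **Masking.** The protocol requires neither a separate examiner nor concealment of earlier acuity results.

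**The concern.** A chart acuity depends on the patient's responses, and also on how far the examiner encourages, how long they wait and when they stop. An examiner who has given the stimulation and can see the previous score knows which line would count as a gain. The same applies at week 0, where the screening value is already on file: a slightly hard reading there enlarges the later change just as a generous reading at week 12 does.

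With no control arm, a shift of this kind enters the week-12 change directly, and no analysis can take it out. The stated purpose is to confirm efficacy, and a two-sided 5% test is planned, so a false positive would matter. The monitoring described under Quality management compares reported data with source records and would not detect a coached reading. Requiring symptoms to be fixed more than 6 months after onset limits spontaneous recovery, which leaves measurement bias as one of the main remaining alternative explanations.

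**Working it through.** The protocol gives no target effect, standard deviation or power calculation, so there is no figure of its own to reproduce. The steps below only show the scale. Gains are written as positive numbers (reductions in logMAR).

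**Inputs from the protocol:** n = 5 eyes; acuity range hand motion to 0.7; an average gain of about 4 ETDRS letters at 12 weeks in the earlier retinitis pigmentosa study (Background).

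**Assumptions:** 0.02 logMAR per letter; a decimal chart in steps of 0.1; SD of the change 0.05 to 0.20 logMAR.

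**1. Benchmark.** 4 × 0.02 = 0.08 logMAR.

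**2. One chart step.** Step = log10(ratio of decimal acuities); shift in the mean = sum of the steps / 5.

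| Step | logMAR | One eye of 5 | Two eyes of 5 |
|---|---|---|---|
| 0.1 to 0.2 | 0.301 | 0.060 | 0.602 / 5 = 0.120 |
| 0.5 to 0.6 | 0.079 | 0.016 | 0.158 / 5 = 0.032 |

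Only the pair of low-acuity eyes exceeds 0.08.

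**3. One 0.1-logMAR line in k eyes.** Shift = 0.1k / 5 = 0.02k. Setting 0.02k = 0.08 gives k = 4 of 5 eyes.

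**4. The same bias in every eye.** The mean moves by the full amount at any sample size: 2 letters give 0.04 and 4 letters give 0.08. The small sample matters only for shifts confined to one or two eyes.

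**5. Effect on the test.** As a simple stand-in for the mixed model, take a two-sided 5% one-sample t test on 5 changes with true effect zero and a constant bias. The noncentrality is bias × √5 / SD; for example 0.04 × √5 / 0.10 = 0.894. The chance of p < 0.05 is:

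| Bias | SD 0.05 | SD 0.10 | SD 0.15 | SD 0.20 |
|---|---|---|---|---|
| 0.04 | 28% | 11% | 7.5% | 6.4% |
| 0.08 | 76% | 28% | 15% | 11% |

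The nominal rate is 5%. The inflation depends heavily on the assumed SD and is modest at the larger values.

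**The case against.** Three stronger readings are tempting, and the documents support none of them.

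- **That one person is assigned both tasks.** The schedule sentence assigns examinations only, treatment by the same roles is implied elsewhere, and clinical tests may be delegated. A non-treating examiner is already possible. One person doing both is permitted, not required.
- **That the bias could match the effect the trial seeks.** No effect sought is stated. The 4 letters come from another disease and from ETDRS acuity, whereas the primary endpoint here is converted decimal acuity. The Background gives no size for the earlier logMAR gain. The 0.08 is an assumed conversion, and most single-eye shifts fall short of it.
- **That masking would remove the bias.** In a single-arm trial every examiner knows that every patient is treated and which visit is the last. With 5 patients and acuity taken at every visit, a returning examiner may also remember earlier scores. Data collection makes medical records the source, and acuity is not among the items sourced from the case report form. Changing the worksheet or EDC display alone would therefore leave earlier values visible.

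It can also be said that open-label status is declared, and that acuity technique may sit in a trial procedure manual that is not shown. The second point limits the claim to what this protocol contains. The first explains why treatment is known, but not why the examiner needs to see the earlier score. Finally, a compulsory second examiner could require staff that a site lacks, so it should not be mandatory.

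**Conclusion.** The point stands as a cheap improvement in conduct, not as an error that invalidates the plan. The protocol allows the treating team to measure its primary endpoint with earlier scores in view, in a design where the resulting bias cannot be separated from a treatment effect.

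The size of that bias is unknown. Equalling the retinitis pigmentosa figure would take about 4 letters in every eye or one line in 4 of 5 eyes; one step in two eyes at decimal 0.1 would exceed it. These comparisons rest on the assumed 0.02 logMAR per letter and an assumed chart in steps of 0.1. The false-positive rates rest also on assumed SDs and a simplified test. The recommendation does not depend on any of these numbers, only on the possibility of bias and the low cost of reducing it.

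**What to change.** In Implementation schedule and procedure, add two requirements for logMAR and ETDRS acuity, at least at week 0 and week 12:

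1. The value is measured and recorded before the examiner opens any earlier acuity result, whether in the worksheet, the EDC or the medical record.
2. Where existing staff allow, the examiner is someone who did not give that patient's stimulation, using the delegation the section already permits. Where no such person is available, requirement 1 still applies.

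State as a limit of the trial that the examiner's knowledge that all patients are treated, possible recall of earlier scores, and the patient's own expectation remain.

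The cost is slight inconvenience in scheduling and record handling for 5 patients at 3 sites. The endpoint, sample size, visits and analysis do not change.

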**Handling when an adverse event occurs**

Adverse events are all unwanted or unintended illnesses or disorders and their signs (clinical test values) that occur to the subject, user or others when using the study device, regardless of whether it has a causal relationship with the study device. Including abnormalities in). However, if it occurs in a person other than the subject, it is limited to the one suspected to be affected by the use of the investigational device.

Existing pathologies (history or complications that existed prior to the study period) will not be treated as adverse events unless they are exacerbated or the frequency of onset increases during the study period. However, if the complication worsens after the investigational device is performed, it will be treated as an adverse event, and the day when the deterioration is confirmed will be the date of occurrence of the adverse event.

A defect means that the condition of the investigational device is not good in terms of quality, safety, performance, etc., such as damage and malfunction, regardless of which stage of design, delivery, storage, or use. Information on defects in clinical trial equipment is hereinafter referred to as defect information.

Device-related adverse events are adverse events for which a causal relationship with the investigational device or procedure cannot be ruled out.

# If the investigator or investigator finds an adverse event or defect, he / she should take appropriate measures immediately, and if he / she discontinues the use of the investigational device or if treatment for the adverse event is required. Inform the subject to that effect. If an adverse event for which a causal relationship with the study device cannot be ruled out has not been recovered at the end or discontinuation of the study, in principle, observation will be continued as much as possible until recovery or improvement. However, this does not apply if the investigator or investigator determines that the effects of this study have disappeared, the safety of the subject is sufficiently ensured, and further follow-up is not necessary.

All adverse events that occur between the start of the study device and the end of the study will be reported regardless of whether there is a causal relationship with the study device, and the adverse events will be observed until the end of the study period (at the time of discontinuation). do. In addition, all adverse events and defect information that have been determined to have a causal relationship with the investigational equipment will be reported until the end of the clinical trial period.

The investigator or investigator shall describe all adverse events and defects that occurred during the above period in the medical record and case report form inconsistently.

**Contents required for evaluation of adverse events and defects**

1) Name of adverse event

As a general rule, the name of the adverse event should be recorded as the diagnosis name / disease name (disease name). If the diagnosis / disease name cannot be specified, or if the investigator or investigator determines that it is appropriate not to use the diagnosis / disease name, the clinical symptom or sign shall be the adverse event name.

2) Date of onset

3) Date of disappearance: Recovery, recovery or disappearance but with sequelae and date in case of death

4) Outcome: Recovery, remission, recovery or disappearance but with sequelae, unrecovered, dead, unknown

5) Treatment (enforcement of clinical trial equipment): No change, discontinuation, not applicable

6) Other treatments: None, drug treatment, etc.

7) Severity: Non-serious, serious

8) Severity: mild, moderate, severe

-Mild: Adverse events that are not considered to interfere with daily life. Example) To the extent that follow-up is possible

-Moderate: Adverse events that may interfere with daily activities. Example) Degree of need for some intervention or treatment

-Severe: Adverse events that may make daily life difficult. Example) To the extent that advanced and intensive treatment and systemic care are required

9) Causal relationship with investigational equipment: Association can be denied, association cannot be denied

1) Defect name

2) Defect confirmation date

3) Date of occurrence

4) Causes and status of problems that may have occurred

5) Measures for defects

6) Presence or absence of adverse events due to the defect

**Causal relationship between adverse event resilience and investigational equipment**

Recovery of adverse events means recovery to a state without adverse events or to a state before the implementation of the investigational device. When determining the causal relationship with the investigational device in an adverse event, the general condition of the subject, complications, concomitant drug / combination therapy, and temporal relationship should be taken into consideration.

・ Association can be denied: When the subject can be explained to be due to other factors before the start of clinical trial equipment or as shown in the following cases.

1) When the adverse event is a known side effect of the combination drug

2) The same adverse event does not occur even if the investigational device is re-performed.

・ Relationship cannot be denied: When the relationship with other factors cannot be clearly defined

